### Recruitment of participants

To identify eligible children for the study, a community census is being conducted in the catchment area of the Centro de Salud 6 de Octubre, which includes rural, peri-urban and urban areas. Rural areas are defined as streets located on the opposite side of the Itaya river from the city of Iquitos, which is a flood prone area without basic services, electricity and drinking water. Peri-urban areas are located on the Iquitos side of the river and extend into the river, with houses on stilts or raft houses that float on the surface of the river. Many of these houses already have electricity and drinking water, and they are usually located around the health center. Another part of the study community is located in the urban area of Iquitos, with concrete houses that all basic services and access to food markets, etc.

For enrollment in rural areas, a sweep strategy will be applied, meaning that we will look for children who meet the inclusion criteria throughout the community. For the peri-urban area homes without an address (located on rafts) we will also apply the same strategy. In the peri-urban and urban area where there are well-defined maps with streets and addresses, we will recruit candidates with numerical codes from the community census based on a random number generator, starting from the first block and then moving forward clockwise to the next block.

Once the first randomly selected child of any age between 2 and 11 years has been recruited, enrollment will continue in the same way until the established strata are completed: age 2 years = 36 children; 3 years = 36 children; 4 years = 36; 5 years = 32 children; 6 years = 33 children; 7 years = 34 children; 8 years = 35 children; 9 years = 36 children; 10 years = 33 children; 11 years = 34 children. Once all the blocks of the study community have been sampled, if the target number of participants for each stratum were not completed, the process will be repeated from the beginning and thus complete the corresponding sample for each age group.

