**Methods:**

We propose to assess the clinical efficacy of Peruvian national guidelines for deworming programs in a prospective observational study conducted in the Amazon River basin area near Iquitos, Peru. Major outcomes to be evaluated include (1) albendazole resistance of intestinal helminths (trichuriasis, ascariasis, hookworm), and (2) frequency of reinfection with intestinal helminths 4 months after treatment with albendazole. Children ages 2–11 years from the Belén District of Iquitos will be identified based on a community census. Following parental informed consent, demographic data, weight, and height will be recorded and a stool specimen for parasitological exam by direct observation and Kato-Katz concentration method, and helminthic egg counts will be collected prior to administration of albendazole, following Peruvian national guidelines. Follow-up stool specimens examined in the same manner will be collected at 20 days, 90 days, and 100 days following initial administration of albendazole, and based on parasites found repeat treatment will be administered in accordance with national guidelines. Real-time multiplex qPCR will be performed on helminth positive samples collected prior to initial deworming and on helminth-positive specimens detected on day 15–20. A total sample size of 380 participants was calculated based on total population in the target group and prevalence estimates of helminth infections and clinical resistance based on recent data.

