### Sample size

Sampling will be carried out throughout the jurisdiction of the 6 de Octubre Health Center, which includes rural, peri-urban and urban areas, with a total potential study population of 3379 children ages 2 to 11 years based on health center databases. Based on this study population of 3379 children aged 2 to 11 years, to measure clinical resistance to albendazole a sample of 380 children was needed. This calculation was made in Epi Info Version 7.2 applying a type I error of 5% and assuming 50% prevalence of helminths in children, 25% frequency of *Trichuris trichiura* in children with helminths, 50% resistance to albendazole based on detection of any helminth in a follow-up sample and adjusting for 10% loss to follow-up for study participants.

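### The age quotas that end enrolment add to 345, not the stated 380, so the 10% allowance for loss to follow-up is never enrolled

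*Protocol article*

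**What the plan says.** The Sample size section takes 3379 children aged 2 to 11 as the study population and says that "to measure clinical resistance to albendazole a sample of 380 children was needed". It lists the assumptions as a 5% type I error, 50% helminth prevalence, 25% *Trichuris trichiura* among infected children and 50% resistance, and says the figure is adjusted for 10% loss to follow-up. The abstract repeats the total: "A total sample size of 380 participants was calculated".

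Recruitment of participants gives the rule that ends enrolment: "enrollment will continue in the same way until the established strata are completed: age 2 years = 36 children". It then gives quotas for ages 3 to 11 of 36, 36, 32, 33, 34, 35, 36, 33 and 34. If some quotas are unfilled after every block has been sampled, the team goes round again to fill those same quotas. The article mentions no enrolment beyond them, no replacement of lost children and no separate quota for the rural or raft-house areas.

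**The concern.** The quotas are the operating instruction for field staff; 380 is the declared size. If the two differ, the recruitment rule decides how many children are enrolled, and the declared size is not reached.

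The shortfall matters most where the numbers are already small. Clinical resistance can be assessed only in children infected at baseline, and species-specific results only in those carrying that species. The final report would also have to explain why the cohort enrolled is not the cohort planned.

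**Working it through.** **1. Sum of the quotas (Recruitment of participants, ages 2 to 11).**
36 + 36 + 36 + 32 + 33 + 34 + 35 + 36 + 33 + 34 = 345.
380 − 345 = 35, and 35/380 = 9.2%.

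**2. Reproducing the plan's 380.**
Inputs from the Sample size section: N = 3379, p = 0.50, 5% type I error (taken as two-sided, z = 1.96), 10% loss. The margin of error d is not stated; 5 points is an assumption.

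Formula for one proportion with finite-population correction:
n = N·p(1−p) / [(d²/z²)(N−1) + p(1−p)]
= 3379 × 0.25 / [(0.05/1.96)² × 3378 + 0.25] = 345.0.

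345 × 1.10 = 379.5, which rounds to 380.

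Other margins do not give either figure:

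| Assumed margin | n before loss | × 1.10 |
|---|---|---|
| 4 points | 510 | 561 |
| 5 points | 345 | 380 |
| 6 points | 247 | 272 |

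With 5 points, one calculation returns both figures in the article: 345 before the loss allowance and 380 after it.

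**3. What is left after 10% loss.**
The infected and *Trichuris* rows apply the plan's own 50% and 25%, so *Trichuris* is 0.5 × 0.25 = 12.5% of evaluable children.

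| | 380 enrolled | 345 enrolled |
|---|---|---|
| Evaluable (× 0.90) | 342 | 310.5 |
| Infected at baseline (× 0.50) | 171 | 155 |
| *Trichuris* (× 0.125) | 43 | 39 |

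**4. Effect on precision (95% half-width at p = 0.50).**
- All evaluable children, with finite-population correction, 1.96·√[0.25/n × (N−n)/(N−1)]: 5.0 points at 342 and 5.3 at 310.
- Infected children, simple binomial, 1.96·√(0.25/n): 7.5 points at 171 and 7.9 at 155.
- *Trichuris*, simple binomial: 15.0 points at 42.75 and 15.7 at 38.8 (unrounded counts).

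**The case against.** There are three fair points on the other side.

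First, the 5-point margin is not in the article, so the account of how 345 arose is an inference. That stands. However, the inference only explains the gap; the gap itself comes from adding ten printed numbers.

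Second, the quotas might be targets for completers, with over-enrolment or replacement set out in a fuller protocol that a journal article need not repeat. This reading does not fit the text. The sentence concerns enrolment, and the only contingency tops up the same quotas. Both totals are also printed in the article, so this is a conflict between stated figures and not a detail left out.

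Third, the consequence is small: about 0.3 points of half-width overall, 0.4 among infected children and 0.7 for *Trichuris*, in an observational cohort whose sample-size section states no power target. That also stands, and it limits how much weight the point carries. In addition, even 380 enrolled leaves only 342 after 10% loss, slightly under 345. To retain 345 the divisor form is needed: 345/0.90 = 383.3, or 384. This is a minor matter beside a shortfall of 35.

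**Conclusion.** The point holds. The recruitment rule enrols 345 children, the Sample size section and abstract state 380, and nothing in the article reconciles them. The difference is 35 children (9.2%), very nearly the whole loss allowance. This conclusion rests on no assumption.

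That the quotas were set on the figure before inflation is very likely, but it depends on the assumed 5-point margin. The figure of about 310 evaluable children uses the plan's own 10% loss. The loss of precision is modest and would not by itself overturn a conclusion. The reason to correct it is that the declared sample size is not the one the enrolment rule delivers.

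**What to change.** Choose one total and use it in all three places.

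- **Keep 380.** Scale each quota by 380/345. For ages 2 to 11 this gives 40, 40, 40, 35, 36, 37, 39, 40, 36 and 37, which add to 380. If the intention is to retain 345 after 10% loss, the total should be 384, and the Sample size section and abstract should say so.
- **Keep the quotas.** Restate the sample size in the Sample size section and abstract as 345 enrolled and about 310 evaluable, with a half-width of about 5.3 points for a 50% proportion overall. This is the only honest option if enrolment has already closed on the printed quotas.

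In either case, state the margin of error used, so that the figure can be reproduced. The first option costs ten corrected numbers and 35 more children to enrol (39 if the total is 384); the second costs one restated figure and its precision.

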## Data and specimen collection (see Fig. 1 for overview of study visits and procedures)

Following informed consent, demographic data will be collected, including housing characteristics, general caregiver information, and information on hygiene and childcare. Weight and height measurements will be performed by a member of the on-site investigation team, and a stool collection container will be provided to the caregiver [19]. Fresh feces (10–20 g) will be collected from each participant and the date and time of specimen collection will be recorded upon retrieval. At the end of the day specimens will be transported to the laboratory in a biological sample transport box with ice at the end of the day, for analyses that will be carried out within the next 24 h.

### Albendazole treatment and clinical follow-up

Following enrollment and initial stool specimen collection, albendazole 400 mg will be administered orally in accordance with Peruvian Ministry of Health guidelines (RM No. 479-2017-MINSA) as part of the universal treatment policy in Peru. Stool samples for the study will be collected three times after the first stool sample is taken. This means that the same procedures will be repeated at 15 to 25 days, 90 to 100 days and at 130 to 140 days (in order to measure resistance and reinfection at 11%, 50% and 75% of the 6-month interval recommended for repeating preventive treatment). If parasites are found in samples after treatment with albendazole, individualized treatment will be administered according to World Health Organization standard of care treatment guidelines [2]. For *Ascaris* and hookworm, albendazole 400 mg will be administered as a single oral dose. For *Trichuris trichiura*, ivermectin 600 µg/kg/day will be administered with albendazole 400 mg, both as single oral doses [20, 21]. For *Strongyloides stercolaris*, Ivermectin 200 µg/kg/day for 2 days will be administered [22–24].

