Herein we describe the protocol for our observational study of a prospectively enrolled cohort to assess clinical resistance to albendazole and reinfection by intestinal helminths in children from the Peruvian Amazon receiving treatment according to Peruvian Ministry of Health treatment guidelines [7], to measure preventive treatment effectiveness for 6 months.

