### Study design (see Fig. 1)

**Fig. 1 Fig1:**
[figure not shown]
Study design

Prospective cohort study of children aged 2 to 11 years, with an individual time of participation of 4 and a half months.

Participants will be boys and girls ages 2 to 11 years who live in the catchment area of the Centro de Salud 6 de Octubre, located in the district of Belén, city of Iquitos, and department of Loreto in Peru.

Inclusion criteria:Parental written informed consent, in addition to the verbal and written assent for children ages 6 to 11 years.No antiparasitic treatment in the prior 3 months [18].Permanent residence in the study community, with no plans to move in the next 6 months.

Major outcomes:Albendazole resistance of intestinal helminths (Trichuriasis, Ascariasis, Hookworm, Strongyloides).Reinfection with intestinal helminths 4 months after treatment with Albendazole.

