### Statistical analysis

Data will be analyzed in Access using Stata, using chi square, Fisher’s exact, and Wilcoxon tests to compare frequencies between groups. To analyze the data from direct observation and quantification by the Kato-Katz method, descriptive statistics will be used, to report the prevalence found in percentages. For the sociodemographic and clinical data of the study population, measures of central tendency and dispersion will be used for the quantitative variables and measures of relative frequency for the qualitative variables. Comparisons will also be made between sample 1, sample 2, sample 3 and sample 4 to determine the positivity of each species of parasite found using the Yates chi-square test, setting a significance level of p < 0.05.

The sociodemographic variables will be compared with the parasite load and presence/absence of parasites, using a multiple logistic regression model (univariate t-test), to determine the variables statistically associated with infection by *Ascaris lumbricoides*, *Trichuris trichiura* and hookworms.

The quantification performed with the Kato-Katz method will be compared with the Ct value (Ct threshold) of the multiplex qPCR, by converting Log10 of the absolute egg count per stool sample, in order to estimate the absolute egg counts in eggs per gram (EPG) in the DNA extractions, using the following formula [33]:$${\text{EPG}}\;{\text{Ascaris}} = 10\left( {{\text{Ct}} - 36.97} \right)/ - 3.489,$$$${\text{EPG}}\;{\text{Trichuris}} = 10\left( {{\text{Ct}} - 36.73} \right)/ - 3.288,$$$${\text{EPG}}\;N.\;americanus = 10\left( {{\text{Ct}} - 35.02} \right)/ - 3.641,$$$${\text{EPG}}\;A.\;duodenale = 10\left( {{\text{Ct}} - 35.02} \right)/ - 3.641.$$

To determine treatment efficacy, the prevalence will be measured before and after receiving treatment and compared using the Yates chi-square test. For calculations of cure rate and intensity of infection obtained from qPCR, only data from positive results before taking the first dose will be included [34].

The cure rate will be measured using the following formula:$$\frac{{\# \;{\text{positive}}\;{\text{for}}\;{\text{helminths}}\;\left( {{\text{pretreatment}}} \right) - \# \;{\text{negative}}\;{\text{for}}\;{\text{helminths}}\;\left( {{\text{post}}\;{\text{treatment}}} \right)}}{{\# \;{\text{cases}}\;{\text{positive}}\;{\text{for}}\;{\text{helminths}}\;\left( {{\text{pretreatment}}} \right)}} \times 100.$$

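### The stated comparison of positivity across samples 1–4 does not estimate reinfection after the initial albendazole dose, because children who test positive are re-treated and uncleared infections are not separated out; the Abstract and body also disagree on the last visit

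*Protocol article*

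**What the plan says.** The Study design section lists as a major outcome "Reinfection with intestinal helminths 4 months after treatment with Albendazole". The section on albendazole treatment and clinical follow-up says of sampling that "the same procedures will be repeated at 15 to 25 days, 90 to 100 days and at 130 to 140 days", and gives the purpose: "in order to measure resistance and reinfection at 11%, 50% and 75% of the 6-month interval". The same section says "If parasites are found in samples after treatment with albendazole, individualized treatment will be administered". This covers any positive post-treatment sample. The re-treatment depends on species and includes ivermectin for *Trichuris* and *Strongyloides*.

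In the Statistical analysis section, the only sentence that uses the third and fourth samples as follow-up measures is "Comparisons will also be made between sample 1, sample 2, sample 3 and sample 4 to determine the positivity of each species", by a Yates chi-square test. Formulas are given for cure rate, intensity and egg reduction; none is given for reinfection.

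On timing, the Abstract says follow-up specimens "will be collected at 20 days, 90 days, and 100 days following initial administration of albendazole". Study design describes a cohort "with an individual time of participation of 4 and a half months". The Background states the aim as "to measure preventive treatment effectiveness for 6 months".

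**The concern.** A positive result at 130–140 days can arise in three ways: an infection that albendazole never cleared, a reinfection, or a reinfection that re-treatment failed to cure. A negative result can come from a child who was never reinfected, or from one who was reinfected by 90–100 days and then cured by re-treatment. Crude positivity by visit cannot tell these apart.

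The time since treatment also varies. At day 135 a child never re-treated is 135 days past the only dose. One re-treated only around day 20 is about 115 days past the latest treatment, and one re-treated around day 95 is about 40 days past it. A child re-treated for one species has also had drug exposure that may affect the others.

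At stake is one of the two major outcomes. A reader wanting to know how often children are reinfected within the programme's dosing interval would get a number that depends on how well re-treatment worked and on how much infection persisted. Separately, if the Abstract's schedule were followed, no sample would exist at 4 months.

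**Working it through.** **1. Visit timing (the plan's own percentages).** Take 6 months as 180 days and a month as 30 days.
- 20/180 = 11.1%, 90/180 = 50.0%, 135/180 = 75.0%. The body's three percentages reproduce, with day 135 as the middle of the 130–140 window.
- 135/30 = 4.5 months, which matches the stated participation time.
- The Abstract's last visit: 100/180 = 55.6%, and 100/30 = 3.3 months. This fits neither the 75% nor a 4-month outcome.

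**2. Children free of infection at about day 20.** Assumptions not in the documents: constant reinfection hazard λ from day 20, complete and immediate detection, visits at days 20, 95 and 135, and all day-95 positives re-treated. Let F be the true cumulative reinfection by day 135.
- λ = −ln(1 − F)/115. For F = 40%, λ = 0.5108/115 = 0.00444 per day.
- Reinfected by day 95: 1 − exp(−75λ) = 28.3%.
- Positive at day 135 if re-treatment cures all: 1 − exp(−40λ) = 16.3%.
- Positive at day 135 if it cures 70%: 0.717 × 0.163 + 0.283 × (0.7 × 0.163 + 0.3) = 23.4%.
- With full cure, F = 20% reads as 7.5% and F = 60% as 27.3%.

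**3. All children, with uncleared infection included.** Further assumptions: hazard from day 0, so λ = −ln(1 − F)/135; 50% infected at baseline (the prevalence in the Sample size section); a fraction r of these not cleared by the first dose; re-treatment of positives at days 20 and 95 with cure probability c. Here F is the risk by day 135 in a child free of infection after the dose. Positivity at successive visits, Δ days apart, follows

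S(next) = (1 − c)S + [1 − (1 − c)S] × [1 − exp(−λΔ)].

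Worked case, F = 30%, r = 50%, c = 50%, so λ = 0.3567/135 = 0.00264:
- Day 20: 0.25 + 0.75 × 0.0515 = 0.289.
- Day 95: 0.144 + 0.856 × 0.180 = 0.298.
- Day 135: 0.149 + 0.851 × 0.100 = 0.234.

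Last-visit positivity for a true F of 30%:

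| Re-treatment cure | r = 0 | r = 50% |
|---|---|---|
| 100% | 10% | 10% |
| 50% | 19% | 23% |
| 30% | 23% | 32% |
| no re-treatment | 30% | 48% |

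Over F of 10–60%, r of 0–50% and c of 30–100%, the ratio of last-visit positivity to F runs from 0.31 (F = 10%, full cure: 0.031/0.10) to 1.86 (F = 10%, r = 50%, c = 30%: 0.186/0.10).

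**4. Size of a clean at-risk group.** From the Sample size section: 380 × 0.9 × 0.50 × 0.25 = 43 children with *Trichuris* at baseline after losses. If the 50% resistance figure is applied to *Trichuris* (an assumption, since it is stated for any helminth), about 21 would be positive at day 0 and then cleared.

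**The case against.** The article never says that reinfection is read from the comparison across samples, still less from sample 4 alone. It describes that comparison as determining positivity, and the body says reinfection is also measured at the earlier visits. A child reinfected by day 95 is recorded as positive at sample 3. The article is condensed, and the full protocol may define reinfection. This stands as a limit on the point: linking the outcome to the comparison is an inference. What remains is that no other analysis shown could yield reinfection, and this one, followed as written, does not.

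A reader might go further and infer that reinfection will be understated and the programme made to look better than it is. The documents do not support that. Uncleared infection pushes crude positivity up, and the Sample size section itself assumes 50% resistance. Step 3 shows ratios on both sides of 1. Understatement follows only for last-visit positivity alone among children who were negative at 15–25 days.

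It can also be said that the stated aim is to evaluate national guidelines and that the Abstract places repeat treatment under them, so re-treatment might belong to the strategy under study. But the outcome is worded as following albendazole, and the body places re-treatment under World Health Organization guidance. Those two passages also need reconciling.

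The visit-day conflict is easy to resolve from the rest of the text, and the 6-month phrase can be read as referring to the programme's dosing interval. Both are wording points, although the first leaves the Abstract at odds with its own 4-month outcome.

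**Conclusion.** The point holds in this form: the stated comparison mixes persistent infection, reinfection and the effect of re-treatment, and so does not estimate reinfection after the initial dose. The direction of the net error is not fixed by the documents. The range of 0.31 to 1.86 times the true risk is illustrative and rests on the constant hazard, complete detection, and the chosen ranges for residual infection and cure. Among children who had cleared by 15–25 days, last-visit positivity alone falls short of cumulative reinfection: 16% to 23% against a true 40%, for re-treatment cure of 100% to 70%. The visit-day contradiction is confirmed by arithmetic. Because a major outcome is affected and the repair is a matter of wording, it should be made before the data are analysed.

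**What to change.** - For each species, take children positive at day 0 and negative at 15–25 days as at risk of reinfection. Report day-0 negatives separately, as new infections.
- Count the first positive at 90–100 or 130–140 days as the event, and report cumulative incidence by a discrete-time or interval-censored method. A child positive at 90–100 days then stays counted whatever the last sample shows.
- Report children positive at both day 0 and 15–25 days as treatment failures, outside that species' reinfection denominator.
- State how a child re-treated for one species is handled for the others, for example censored at re-treatment, with a sensitivity analysis without censoring.
- Keep the comparison across samples 1–4 as a description of positivity by visit, labelled as such.
- Reconcile the Abstract's visit days with the body. The 75% figure and the 4.5-month participation both fit a last visit near day 135. Reword the 6-month aim to match the follow-up actually observed.

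This changes no treatment and adds no visit. The cost is a smaller denominator, perhaps about 21 children for *Trichuris* under step 4, and fewer once censoring applies, so intervals for that species will be wide. An infection missed at 15–25 days would still be counted as a reinfection; the report should say so.
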